**March, 2010**

# 1. Purpose of the Study

Dementia, which increases with age, disrupts the life of both the patient himself and his family and requires substantial treatment and elderly nursing costs, so establishing methods to prevent and treat it has become an urgent task. Especially when considering the rapidly changing demographics of Japan, the problems involved in dementia are becoming an increasingly important issue. Currently, no radical treatment has been established for Alzheimer's disease and cerebrovascular disease, which are the primary causative diseases of dementia, and so initiatives for preventing dementia or delaying its onset play an important role as countermeasures to dementia.

A state that is not dementia but rather a mild cognitive decline is called "mild cognitive impairment" (or "MCI"), which has attracted attention as a preliminary stage for preventing dementia. A large-scale epidemiological study focusing on community-dwelling elderly in Japan put the prevalence of MCI at roughly 5% to 7%. It was reported that 3.7% of these community-dwelling elderly people with MCI transitioned to dementia within three years, whereas 0.2% of elderly people who did not have MCI developed dementia. Also, because 38.5% of cases of MCI return to normal after five years [[1](#_ENREF_1)], initiatives to mitigate MCI are important in order to prevent dementia.

Approaches to mitigate MCI and prevent the onset of dementia have made use of drug therapy, the purpose of which is to eliminate risk factors and delay onset, as well as non-drug therapy, which has included improvements in lifestyle habits. Examples of drug therapies include administering drugs for hypertension, hyperlipidemia, and diabetes, which are risk factors for Alzheimer's disease and cerebrovascular disease, or prescribing donepezil hydrochloride in order to delay the onset of Alzheimer's-type dementia. However, the direct effects of drug therapy to eliminate risk factors are difficult to grasp, and donepezil hydrochloride can be expected to have only a limited effect [[2](#_ENREF_2)].

Examples of non-drug therapies used to intervene in order to prevent dementia include promoting habitual physical activity [[3](#_ENREF_3),[4](#_ENREF_4)], eating foods high in antioxidants and/or anti-inflammatory ingredients [[5](#_ENREF_5)], and participation in social and intellectual activities [[6](#_ENREF_6)], which have been recognized as protective factors against the onset of dementia. In particular, many findings have been noted regarding a connection between aerobic exercise and preventing the onset of Alzheimer's disease, and the results of a recent randomized control trial have been reported as providing verification of the efficacy of exercise for elderly adults with MCI [[7](#_ENREF_7)]. In that study, 152 participants were randomly assigned to an aerobic exercise group and a non-aerobic exercise group, and to a vitamin B group and a placebo group, and a one-year intervention was carried out. The participants exercised twice weekly, for 60 minutes each time. For aerobic exercise, they trained walking together in groups. The results showed that aerobic exercise has no significant effect in improving cognitive function. However, these results were based on an intention-to-treat analysis, which included 30 participants who did not attend the exercise sessions. If only those elderly adults who had a high attendance rate among the aerobic exercise group are included in the analysis, then the results show increased memory and attentiveness, confirming the effectiveness of aerobic exercise in elder adults with MCI, though only to a limited extent. In another recent report, when elderly adults with MCI (a mean age of 70 years) participated in aerobic exercise four times every week over the course of six months with a heart rate reserve of 75% to 85%, the results showed that executive function was significantly improved [[8](#_ENREF_8)].

Exercise thus serves as a potential mechanism with a favorable effect on cognitive function, and, findings from animal studies especially have suggested that it reduces nerve inflammation, promotes angiogenesis, helps regulate the neuroendocrine response, and reduces amyloid accumulation. A recent study on humans has also reported that six months of aerobic exercise increased the capacity in the regions of the brain associated with lowered cognitive function caused by aging [[9](#_ENREF_9)]. This is thought to be due to the fact that aerobic exercise leads to angiogenesis and increases the flow of blood to the brain [[10](#_ENREF_10)].

Given the background of these studies, it is an object of the present study to examine whether it is possible for exercise to also improve cognitive function in elderly adults with MCI. The present study further seeks to use a randomized controlled trial to verify whether improved brain capacity and brain function are observed in tandem with functional changes.

# 2. Participants

This research project seeks to validate the effect of exercise intervention in order to validate the effect of improved cognitive function in elderly adults with MCI. Elderly adults over the age of 65 who speak Japanese as their native language will be randomly assigned to either a control group or an exercise-intervention group. Participants who are found to have amnestic MCI will be subjected to randomized, stratified allocation in which they are assigned into either an Exercise Group 1 of people who agree to have their brain function measured by positron emission tomography (PET) testing or near infrared spectroscopy (NIRS), or into an Exercise Group 1 of the other elderly adults with MCI.

The reason why it is necessary to randomly allocate the participants is that the effect of intervention cannot be validated if the influence on cognitive function of unknown factors other than intervention is not equalized among the groups, and high-quality scientific evidence cannot be obtained without this technique.

In terms of ethical issues for the participants in the random allocation of the participants, due consideration must be given in general in the practice of health services for the elderly to ensure that all residents have equal access to appropriate services. The elderly adults with MCI who will be considered as candidate participants in this research project are a population that, having been diagnosed with MCI, requires some form of action. However, because there currently is a lack of any sufficiently clear and effective method for mitigating MCI with non-drug intervention, we find ourselves in a situation where it is not possible to decide what appropriate services would be. Therefore, at this point in time, randomly allocating the participants has the potential to incur advantages and disadvantages in each group; if this comes to be better understood and there is thus a desire to conduct a research project, we feel that ethical considerations can be avoided. However, it is necessary to proceed with the present research project under the assumption that, in the event that the effects of intervention are confirmed, a similar intervention will immediately be provided to the control group. The effects of intervention must be judged on the comprehensive observation of trends in evaluation indices conducted six months and 12 months after intervention is begun.

## 2-1. Participant Inclusion Criteria

The criteria for participant inclusion will be that participants must be elderly adults over the age of 65 who had a clinical dementia rating (CDR) of 0.5 in an epidemiological study conducted in Ōbu City (contributing researcher: [name]) with the aid of the Ministry of Health's 2009 Grant-in-Aid for Scientific Research (anti-dementia general research projects) or who received a specific health examination in Ōbu City in 2009 and have had problems with subjective memory. Participants will sign a written agreement; participants who are deemed incapable of giving consent will be allowed to participate under the condition that a family member or relative agree to sign as legal representative.

The participants included in Exercise Group 1 are patients with amnestic MCI. The criteria for amnestic MCI follows the criteria of the Japan-Alzheimer’s disease neuroimaging initiative (J-ADNI) shown below.

Criteria for Amnestic MCI

**Type I**: The patient complains of own memory impairment + People in the position of caregivers (family) accept this

**Type II**: The patient does not complain of own memory impairment, but rather the existence of the memory impairment is indicated by the caregivers (family).

Note: This excludes cases in which only the patient complains of memory impairment and people in the position of caregivers (family) do not accept this.

MMSE is from 24 to 30 points.

The cut-off scores with the Wechsler memory Scale-R/Logical memory II are as follows, considering how many years of education the patient has had.

0-9 years of education: 2 points or less

10-15 years of education: 4 points or less

16 or more years of education: 7 points or less

CDR is 0.5. The patient must not suffer from depression.

## 2-2. Participant Exclusion Criteria

1. Patients with Parkinson's disease, multiple cerebral infarction, Huntington's disease, normal pressure hydrocephalus, brain tumor, progressive supranuclear palsy, epilepsy, subdural hematoma, multiple sclerosis, head trauma with lingering delayed effects, or diabetes.

2. Patients found by MRI at the time of screening to have an infection, or a localized lesion such as cerebral infarction that will affect cognitive function.

3. Patients who have received a pacemaker, an aneurysm clip, a prosthetic valve, a cochlear implant, or any other kind of metal in the body.

4. Patients who have major depression, bipolar disorder, a history of alcoholism or other kind of drug-dependence, or severe or unstable disease.

5. Patients who have a vitamin B12 or folic acid deficiency, syphilis, or abnormal thyroid function.

6. Patients who are participating in a drug trial for a novel AD drug treatment.

7. Patients under the age of 85 who are found to have significant functional decline in motor function testing and for whom performing the exercise intervention is deemed to be a challenge.

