## 2-3. Allocation of Participants

Participants will go through three rounds of testing for 1) CDR score and subjective memory impairment, 2) cognitive function and motor function, and 3) MRI photography, following which they will be randomly allocated to a control group and an exercise group. Prior to this allocation, elderly adults with amnestic MCI will be categorized to perform a stratified allocation. The method for allocating participants involves having experts, who knew neither the study content nor the participants, randomly assign participants into equally sized groups using a computer program, which they will do while blinded.

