### 4-1-2. Aerobic exercise

Duration: about 30 minutes

The aerobic exercise is designed to focus on walking and stair training. The aerobic exercise will be performed over about 20 to 30 minutes per class. Referring to previous studies [[8](#_ENREF_8),[11](#_ENREF_11)] that carried out an aerobic exercise intervention for elderly adults with MCI, the objective is to start from a heart rate reserve load of 40% to 50% and gradually increase intensity over the course of six weeks to reach an exercise intensity of 75% to 85% heart rate reserve after week 7 (Table). The exercise intensity is set by the physiotherapists, who will use the Karvonen method [[12](#_ENREF_12)] to set the exercise intensity based on heart rate reserve, and also will refer to the rated perceived exertion (or "RPE") of the participants to adjust the exercise intensity in consideration of their safety. The participants' pulses will also be monitored and managed during exercise.

The content of the aerobic exercise draws on ordinary indoor and outdoor walking as well as step training (using a bar or ladder). It will also adopt an aerobic exercise (double challenge) program incorporating a cognition challenge which, when combined with the exercise, is expected to activate brain activity.

In the special case of adults who are taking a β-blocker, their medications status will be checked in advance, and their exercise intensity will be studied on an individual basis rather than being set based on heart rate.

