**Name：**

Anamnesis

Current medical history

【Medication】

| Antihypertensive | （ □No □Yes ） |
| --- | --- |
| Stabilization agent | （ □No □Yes ） |
| Sleep agent | （ □No □Yes ） |
| Cardiac medication | （ □No □Yes ） |
| Cerebral medication (circulation or metabolism) | （ □No □Yes ） |
| Diabetes or hyperlipidemia drags | （ □No □Yes ） |
| Antidepressant agent | （ □No □Yes ） |
| Antipsychotic agent | （ □No □Yes ） |
| Ginkgo biloba | （ □No □Yes ） |
| Others |  |

Dominant hand

Right / Left

Drug allergy

No / Yes（　　　　　　　　　　　　　　　　　　　　　　）

Medical history

| Any operation | （ □No □Yes ） |
| --- | --- |
| Cardiac pacemaker or prosthetic valve | （ □No □Yes ） |
| Artificial ear | （ □No □Yes ） |
| Metal fragment in the body | （ □No □Yes ） |
| Blood vessel prosthesis | （ □No □Yes ） |
| Operation of cerebral aneurysm | （ □No □Yes ） |
| Parkinson’s disease | （ □No □Yes ） |
| Multiple infarction | （ □No □Yes ） |
| Huntington's disease | （ □No □Yes ） |
| Normal pressure hydrocephalus | （ □No □Yes ） |
| Brain cancer | （ □No □Yes ） |
| Progressive supranuclear palsy | （ □No □Yes ） |
| Epilepsia | （ □No □Yes ） |
| Subdural hematoma | （ □No □Yes ） |
| Multiple sclerosis | （ □No □Yes ） |
| Head trauma | （ □No □Yes ） |
| Other brain disease | （ □No □Yes ） |
| Diabetes | （ □No □Yes ） |
| Depression or bipolar disorder | （ □No □Yes ） |
| Alcohol or drug dependence | （ □No □Yes ） |
| Deficiency of VB12 or folic acid | （ □No □Yes ） |
| Lues venerea | （ □No □Yes ） |
| Thyroid dysfunction |  |
| Medication for Alzheimer’s disease |  |

Inhibition of exercise from a primary care doctor

No / Yes（reason: ）

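### Exclusion 7 applies only below age 85, so as written a person aged 85 or over with the same motor findings remains eligible

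*Protocol*

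**What the plan says.** Item 7 of Protocol section 2-2 (Participant Exclusion Criteria) removes "Patients under the age of 85 who are found to have significant functional decline in motor function testing". The same sentence adds a further condition that must also be met: "and for whom performing the exercise intervention is deemed to be a challenge". It is the only exclusion that refers to motor function.

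On age, section 2-1 requires that "participants must be elderly adults over the age of 65". Section 2 gives the same lower bound. Neither section gives an upper bound.

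On timing, section 2-3 states: "Participants will go through three rounds of testing for 1) CDR score and subjective memory impairment, 2) cognitive function and motor function", then MRI, and only then random allocation. The motor result is therefore known for every candidate before allocation, whatever their age.

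On the programme, section 4-1-2 aims to "reach an exercise intensity of 75% to 85% heart rate reserve after week 7". The same section has physiotherapists refer to the perceived exertion "of the participants to adjust the exercise intensity in consideration of their safety", and pulses are monitored during exercise. Section 4-1 adds a check of vital signs before each class and individual support from the physiotherapists.

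**The concern.** The evident purpose of item 7 is to keep out people whose motor function makes the exercise programme too hard for them. The age phrase limits that protection to people under 85 and so leaves out the oldest candidates. Two people with identical motor findings, both judged to find the programme a challenge, are treated differently because one is 84 and the other 85, and it is the older one who stays eligible.

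Two things are at stake. The first is participant safety: staff who apply the text literally could enrol someone whom the criterion seems meant to remove. The second is clarity about the trial population: the document does not show whether the trial is meant to have an upper age limit, or a motor-function limit that applies at all ages.

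**Working it through.** The plan gives no figure for this point. The check is one of logic, followed by an illustrative bound on size.

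**1. Structure of item 7.** The clause joins its conditions, so

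excluded by item 7 = (age under 85) AND (significant motor decline) AND (exercise deemed a challenge).

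| Age | Motor decline | Exercise deemed a challenge | Excluded by item 7? |
| --- | --- | --- | --- |
| 84 | yes | yes | yes |
| 84 | yes | no | no |
| 85 or over | yes | yes | no |
| 85 or over | yes | no | no |

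The first and third rows differ only in age. The second row matters too: motor decline alone excludes nobody, even below 85.

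**2. Does anything else close the gap?**

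- Upper age limit: none in section 2 or 2-1.
- Exclusions 1 to 3: named neurological diseases and diabetes, MRI findings, and implants or metal. Some of these diseases may coincide with motor decline, but the ground for exclusion is the disease and not the motor test.
- Exclusion 4: psychiatric disorder, dependence, or "severe or unstable disease". This is a general disease criterion and does not refer to motor testing.
- Exclusions 5 and 6: deficiency, syphilis or thyroid abnormality, and participation in a drug trial.

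None of these acts on motor decline. A person in the third row of the table who meets the other criteria can go forward to allocation under section 2-3 and may be assigned to exercise.

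**3. Size.** Inputs: 50 participants in the intervention group (table in section 4-1); *a*, the share aged 85 or over, not given; *p*, the share of those who meet both other conditions, not given.

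Number affected in the exercise arm = 50 × *a* × *p*.

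- Assume *a* = 5%: 50 × 0.05 = 2.5, times *p*.
- Assume *a* = 10%: 50 × 0.10 = 5, times *p*.

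Since *p* lies between 0 and 1, the result runs from 0 up to 2.5 (at *a* = 5%) or 5 (at *a* = 10%). The figures 2.5 and 5 are ceilings, reached only if everyone aged 85 or over also has significant decline and is judged to find the exercise a challenge.

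**The case against.** The strongest reply is that this is one loosely worded age phrase affecting an unknown and possibly empty subgroup. The heart rate target is an objective and not a fixed requirement. Vital signs are checked before each class, pulses are monitored, aerobic intensity and strength loads are adjusted using perceived exertion (sections 4-1 to 4-1-3), and section 7 provides for discontinuation. Eligibility is settled before randomisation, so anyone admitted by the wording can fall in either arm, and comparability at entry is not harmed. No estimate, test or sample size is shown to be affected. The phrase may also be a slip of drafting or translation.

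Most of this stands and limits the weight of the point. It does not remove it, because safeguards in class act after enrolment and do not decide who is enrolled. If the phrase is a slip, the text still needs correcting, since nothing in the document says what was meant.

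A reader might infer three stronger things that the document does not support:

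- **That every candidate aged 85 or over is affected.** Only those who also meet both other conditions are.
- **That the wording causes dropout in the exercise arm alone.** Poorer class attendance among such people is plausible but not shown, and controls also have to return for testing at 6 and 12 months.
- **That a further exclusion is missing because the Appendix 1 questionnaire records "Inhibition of exercise from a primary care doctor".** That is an item on a data form which also records things that match no exclusion, such as drug allergy. The schedule does not name the form, so its completion before allocation is an inference.

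**Conclusion.** The point holds as a defect of wording. Read literally, item 7 cannot exclude anyone aged 85 or over, no other criterion covers the same ground, and the rule therefore works against its own evident purpose for the oldest candidates. This conclusion rests only on the text of sections 2, 2-1, 2-2 and 2-3 and needs no numerical assumption.

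The practical size is unknown, probably small and possibly nil. The ceiling of 2.5 to 5 people in the exercise arm depends wholly on the assumed 5% to 10% share aged 85 or over. No bias in the treatment comparison is demonstrated. The case for correction rests on participant safety, on an unambiguous definition of the population, and on the very low cost of the change. The document does not settle whether an upper age limit or an age-free motor criterion was intended, and this review does not choose between them.

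**What to change.** Reconcile item 7 of section 2-2 with the open-ended age range in sections 2 and 2-1, so that the age phrase does not exempt the oldest candidates from the motor-decline exclusion. Two forms of wording would do this:

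- if an age limit was meant, separate it from the motor condition and state it as an item of its own; or
- if no age limit was meant, remove the age qualifier from item 7.

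The sponsor's clinicians decide which was intended. Under section 16 a change to the implementation plan needs prior approval from the ethical review committees.

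The cost is one line of eligibility wording and at most a few fewer eligible candidates. No new assessment is needed, because motor function is already tested before allocation.

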## 2-3. Allocation of Participants

Participants will go through three rounds of testing for 1) CDR score and subjective memory impairment, 2) cognitive function and motor function, and 3) MRI photography, following which they will be randomly allocated to a control group and an exercise group. Prior to this allocation, elderly adults with amnestic MCI will be categorized to perform a stratified allocation. The method for allocating participants involves having experts, who knew neither the study content nor the participants, randomly assign participants into equally sized groups using a computer program, which they will do while blinded.

# 3. The Survey

The following table lists the sequence before and after intervention in which, for each patient, blood is sampled, cognitive function is tested, motor function is tested, vital function is examined, the brain is CAT-scanned, and - in some adults - brain activity is measured by NIRS and a PET scan is taken.

**Study Measurement Schedule**

３—１．Exercise Group 1

| Items | Screening | BL | 6M | 12M |
| --- | --- | --- | --- | --- |
| Explain study & obtain consent | X | X |  |  |
| Screening of inclusion and exclusion criteria | X | X |  |  |
| Medical interview | X | X | X | X |
| Vital sign |  | X | X | X |
| MMSE | X | X | X | X |
| CDR | X | X | X | X |
| Wechsler memory Scale-R/  Logical Memory |  | X | X | X |
| Digit span |  | X | X | X |
| Stroop color word test |  | X | X | X |
| Digit symbol substitution |  | X | X | X |
| Category Fluency |  | X | X | X |
| Trail making test A and B |  | X | X | X |
| Geriatric Depression Scale |  | X | X | X |
| Clock Drawing |  | X | X | X |
| ADAS-Cog |  | X | X | X |
| Physical performance |  | X | X | X |
| TMIG index |  | X | X | X |
| Basic ADL |  | X | X | X |
| Life-space assessment |  | X | X | X |
| SF-8 |  | X | X | X |
| MRI（1.5T） |  | X | X | X |
| NIRS |  | X | X | X |
| FDG-PET |  | X | X | X |
| Blood sampling |  | X | X | X |
| Payment for participants with neuroimaging tests |  | X | X | X |
| Check harmful event |  | X | X | X |
| Check self-monitoring exercise |  |  | X | X |

３—２．Exercise Group 2

| Items | Screening | BL | 6M | 12M |
| --- | --- | --- | --- | --- |
| Explain study & obtain consent | X | X |  |  |
| Screening of inclusion and exclusion criteria | X | X |  |  |
| Medical interview | X | X | X | X |
| Vital sign |  | X | X | X |
| MMSE | X | X | X | X |
| CDR | X | X | X | X |
| Wechsler memory Scale-R/  Logical Memory |  | X | X | X |
| Digit span |  | X | X | X |
| Stroop color word test |  | X | X | X |
| Digit symbol substitution |  | X | X | X |
| Category Fluency |  | X | X | X |
| Trail making test A and B |  | X | X | X |
| Geriatric Depression Scale |  | X | X | X |
| Clock Drawing |  | X | X | X |
| ADAS-Cog |  | X | X | X |
| Physical performance |  | X | X | X |
| TMIG index |  | X | X | X |
| Basic ADL |  | X | X | X |
| Life-space assessment |  | X | X | X |
| SF-8 |  | X | X | X |
| MRI（1.5T） |  | X | X | X |
| NIRS |  | X | X | X |
| FDG-PET |  | X | X | X |
| Blood sampling |  | X | X | X |
| Payment for participants with neuroimaging tests |  | X | X | X |
| Check harmful event |  | X | X | X |
| Check self-monitoring exercise |  |  | X | X |

３—３．Control Group

| Items | Screening | BL | 6M | 12M |
| --- | --- | --- | --- | --- |
| Explain study & obtain consent | X | X |  |  |
| Screening of inclusion and exclusion criteria | X | X |  |  |
| Medical interview | X | X | X | X |
| Vital sign |  | X | X | X |
| MMSE | X | X | X | X |
| CDR | X | X | X | X |
| Wechsler memory Scale-R/  Logical Memory |  | X | X | X |
| Digit span |  | X | X | X |
| Stroop color word test |  | X | X | X |
| Digit symbol substitution |  | X | X | X |
| Category Fluency |  | X | X | X |
| Trail making test A and B |  | X | X | X |
| Geriatric Depression Scale |  | X | X | X |
| Clock Drawing |  | X | X | X |
| ADAS-Cog |  | X | X | X |
| Physical performance |  | X | X | X |
| TMIG index |  | X | X | X |
| Basic ADL |  | X | X | X |
| Life-space assessment |  | X | X | X |
| SF-8 |  | X | X | X |
| MRI（1.5T） |  | X | X | X |
| NIRS |  | X | X | X |
| FDG-PET |  | X | X | X |
| Blood sampling |  | X | X | X |
| Payment for participants with neuroimaging tests |  | X | X | X |
| Check harmful event |  | X | X | X |

